## Abstract

**ABSTRACT:**

**Introduction:**

The prevalence of neural tube defects (NTDs) is higher in Ethiopia than most other countries, and ~84% of Ethiopian women of reproductive age (WRA) have folate insufficiency, a major risk factor for NTDs. Salt fortification with folic acid is a potential strategy to improve women’s folate status, but data are needed on the acceptability, nutritional impact and safety of folic acid fortification of iodised salt.

**Methods and analysis:**

The study is designed as a community-based, household-randomised, dose–response trial. A total of 360 non-pregnant WRA 18–49 years of age will be randomly assigned to one of three intervention arms: (1) iodised salt fortified with 30 ppm folic acid to provide ~200 µg folic acid/day; (2) iodised salt fortified with 90 ppm folic acid to provide ~600 µg folic acid/day; or (3) iodised salt (comparator). The preweighed salts will be delivered to participants’ homes biweekly for 26 weeks; unused salt will be collected and weighed. Fasting, venous blood samples will be collected at baseline, end line and a randomly assigned intermediate time point for assessment of folate, iodine, vitamin B_12_ and other micronutrient status biomarkers. Women’s dietary intakes, including discretionary salt consumption, will be measured using weighed food records; 24-hour urine specimens will be analysed for sodium and iodine excretion. Primary outcomes are women’s consumption of study salts, change in biomarkers of folate and iodine status and prevalence of adverse events. Results will be analysed using analysis of covariance models to estimate group mean differences for continuous outcomes, controlling for baseline measurements, and log-binomial or modified Poisson regressions for categorical outcomes. Prespecified effect modifications will be explored.

**Ethics and dissemination:**

The study has been approved by the Ethiopian Public Health Institute’s Institutional Review Board, and the protocol has been registered with ClinicalTrials.gov (registration number NCT06223854). Study results will be published in open access scientific journals and disseminated nationally in Ethiopia.

**Trial registration number:**

NCT06223854.

Strengths and limitations of this studyRandomised intervention design.Adequate sample size to detect important differences by study arm.Multiple methods for assessing adherence, impact on folate and iodine status and possible adverse effects.Exploratory analyses of possible modifying effects of initial folate and vitamin B_12_ status, genetic polymorphisms, household food insecurity and other baseline characteristics.Inability to assess the effects of the intervention on household members other than women of reproductive age; and exclusion of women who are pregnant or have selected illnesses, which undermines possible extrapolation of study results to these population subgroups.

## Introduction

 The prevalence of neural tube defects (NTDs) in Ethiopia is very high relative to other countries, as described in more detail below. One of the most widely recognised and important causes of these devastating abnormalities is maternal folate insufficiency during the early weeks of pregnancy. This research project is designed to assess the effects of fortifying iodised salt (IS) with folic acid to improve women’s folate status and thereby reduce the risk of NTDs. Folic acid is a synthetic, relatively stable, oxidised form of folate (vitamin B_9_, pteroylmonoglutamate), which can be converted to reduced folate in the body. The present manuscript summarises information on the planned intervention trial, as described in detail in the master protocol (version 7, dated 16 January 2024), which covers both the previously completed, preliminary studies and the currently presented intervention trial.

NTDs, including anencephaly and spina bifida, are malformations of the brain and spinal cord which can result in spontaneous abortions, elective termination of pregnancy, stillbirths and long-term disabilities, including hydrocephalus and related central nervous system infections.^1^ In lower resource settings, approximately three-fourths of NTD-affected newborns die before the age of 5 years.^2^ Recent analyses indicate that an estimated 260 100 pregnancies worldwide were affected by NTDs in 2015, equivalent to a prevalence of 18.6 per 10 000 live births.^2^ The prevalence of NTDs is strikingly higher in Ethiopia than the global average. Two recent meta-analyses of hospital-based studies found a mean birth prevalence of 63.3 per 10 000 (95% CI 50.9, 75.7) and 59.7 per 10 000 (95% CI 42.1, 84.7),^3 4^ and one hospital-based study in Addis Ababa, which also included pregnancy terminations, found a prevalence of 127.9 per 10 000 pregnancies after 12 weeks of gestation.^5^ One study of the causes of fetal and young child deaths in eastern Ethiopia found that NTDs were the second leading cause of stillbirths, accounting for 17% of the 114 stillbirths examined.^6^

NTDs can be induced by environmental exposures, such as undernutrition and xenobiotics, genetics or a combination of these causes. There is considerable evidence from observational studies and intervention trials that low maternal folate status during the periconceptional period is a primary risk factor for NTDs.^7^,^9^ A meta-analysis of the effects of periconceptional oral folate supplementation (≥400 µg/day) that included four trials and 6708 births found that daily folic acid supplementation (alone or in combination with other vitamins and minerals) reduced the incidence of NTDs by 69% compared with no intervention, placebo or vitamins and minerals without folic acid.^10^ WHO guidelines state that red blood cell (RBC) folate concentrations can be used as an indicator of NTD risk at the population level, and WHO recommends that the RBC folate concentration of all women of reproductive age (WRA) should be greater than 906 nmol/L to minimise the risk of folate-related NTDs.^11^ This cut-off is equivalent to a cut-off of 748 nmol/L using the updated microbiological assay supported by the US Centers for Disease Control and Prevention (CDC).^12^ In Ethiopia, 84% of WRA have an RBC folate concentration less than this cut-off.^13^

In 1992, the US Public Health Service stated that all women who are capable of becoming pregnant should consume 400 µg folic acid per day to reduce their risk of having an NTD-affected pregnancy,^14^ and the US Preventive Services Task Force subsequently recommended supplementation with 400–800 µg folic acid per day.^15^ However, because maternal folate status must be sufficient before conception to prevent NTDs, as well as the facts that many pregnancies are unplanned and adherence to daily supplementation over decades is very challenging, food fortification has been proposed as a better option to deliver additional folic acid. In 1998, the US Food and Drug Administration (FDA) began mandating folic acid fortification of enriched grain products (140 µg folic acid/100 g), with a primary focus on wheat flour fortification.^16^ In 2009, WHO recommended fortification of cereal flour with folic acid to prevent NTDs, with proposed fortification levels ranging from 100 µg to 500 µg of folic acid per 100 g flour (1–5 ppm), depending on the amount of usual flour consumption by the target population.^17^ A total of 69 countries now have fortification standards for the inclusion of folic acid in wheat and/or maize flour.^18^ Notably, studies in multiple countries have consistently shown that the prevalence of NTDs declined following the implementation of folic acid fortification programmes.^19^

Flour fortification is not a viable option to achieve high folic acid coverage in Ethiopia, as only 39% of the wheat flour is industrially produced^18^; and, according to preliminary results from the latest national food consumption survey, only 30% of women have access to fortifiable cereal flour.^20^ Thus, other potential fortification vehicles need to be considered. The Ethiopian government has mandated salt iodisation since 2011, and almost all households now have access to IS.^20^ The Ethiopian FDA has authorized 19 salt iodisation plants, with a total production capacity of 228 000 tons of salt per month.^21^ The iodisation process employs spray technology to apply potassium iodate solution to achieve a target iodine concentration of 30–40 ppm in salt. Research indicates that it is technically feasible to combine folic acid in the same spray solution used for salt iodisation, and the fortificants are stable in the finished salt for at least 12 months.^22^ Preliminary studies have found that double-fortified salt (DFS) containing iodine and folic acid (IoFA) is generally acceptable in both rural and urban Ethiopian communities ([name], unpublished). Thus, it should be possible to build on the existing salt iodisation programme to deliver folic acid.

Recognising the alarmingly high prevalence of NTDs and the high prevalence of folate insufficiency, in 2019 the Ethiopian government published a set of recommendations on specific approaches to improve women’s folate status.^23^ Among the proposed activities, the government indicated that salt fortification may be considered as an alternative to wheat flour fortification; but information is needed on the acceptability, effectiveness and safety of salt fortification with folic acid. The current study is designed to fill this information gap. The main objectives of the study are to assess among non-pregnant Ethiopian WRA: (1) the acceptability and intake of DFS containing IoFA, compared with IS; (2) the effects of DFS on biomarkers of folate and iodine status; and (3) the occurrence of any serious adverse events in relation to salt type.

## Methods and analysis

### Study design, study site and randomisation

The study is designed as a prospective, community-based, triple-blind, dose–response trial. Non-pregnant women and their households will be randomly assigned at the household level to one of three intervention arms using the Moses-Oakford block randomisation algorithm.^24^ Participant identification numbers will be assigned sequentially by the field team, as described below.

The study team will monitor the women’s salt consumption, but will not control their intakes, so the study is viewed as a ‘hybrid’ efficacy/effectiveness trial. The trial is designated as such because the protocol does not employ a true efficacy design (in which salt intakes would be controlled), nor does it conform to a true effectiveness design (in which the participants would acquire the salt independently under usual market conditions).

The study salts will be coded by participant identification number, and the study participants, data collectors, laboratory and data analysts, and investigators will not be informed of the group identity until data collection and preliminary analyses are completed. However, because of subtle changes in the colour of the folic acid-fortified salts due to the natural yellow hue of folic acid, it may be possible to discern differences in the folic acid-fortified versus non-folic acid-fortified study salts in the participants’ homes. Nevertheless, all clinical specimens will be coded before submission to the laboratories, and the group identity will be concealed from the laboratory technicians and from the data analysis team during the initial stages of data analysis. Participants’ study arms and the identity of the salt types will be revealed only after preliminary analysis of data and following agreement of the co-principal investigators (PI) on the interpretation of study outcomes.

The primary endpoints of the trial are: (1) biweekly disappearance of project-supplied salt from the household; (2) discretionary salt consumption by WRA, as measured by direct observation during in-home weighed food records; (3) changes in markers of folate status (RBC and serum folate, serum homocysteine); (4) changes in markers of iodine intake and status (urinary iodine excretion, serum thyroglobulin); and (5) period prevalence of serious adverse events (SAE). Secondary outcomes include qualitative assessments of salt acceptability, changes in haematological status (haemoglobin (Hb), RBC indices and leucocyte morphology) and possible adverse effects, as assessed from participant reports and by selected metabolic indicators (insulin resistance and metabolomic responses). Possible modifying effects of the intervention that will be explored are: (1) household food insecurity; (2) biomarkers of initial folate, vitamin B_12_ and riboflavin status; and (3) polymorphisms of the genes coding for methylenetetrahydrofolate reductase (MTHFR) and serine hydroxymethyltransferase 1 (SHMT1), which may affect the metabolism of folic acid. We will also assess the effect of free distribution of salt on women’s discretionary salt consumption by monitoring salt intakes and 24-hour urinary sodium excretion before and during the trial.

The study will take place in two rural and two semiurban communities of Gimbichu *woreda*, Oromia Region, Ethiopia (altitude ~2450 m above sea level; figure 1). The total population of the *woreda* is 67 773, of whom ~27% are WRA. According to a preliminary study in the project area, WRA consume a median of 6.6 g discretionary salt per day (95% CI 4.1, 10.2), and, on average, households use approximately 30–47 g salt per day, depending on household size.^25^ A total of 360 eligible women will be randomly assigned to receive one of the three study salts using a block randomisation process.^24^ Based on preliminary studies, salt sharing between households is uncommon, and residents of the study communities are not consuming folic acid-fortified flour ([name], unpublished).

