**Figure 1 F1:**
[figure not shown]
Location of study communities: Gimbichu *woreda*, Oromia Region, Ethiopia.

The intervention was initiated on 30 April 2024 and data collection should be completed by mid-December 2024.

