### Informed consent, institutional review board approval and trial registration

For the initial home visit to screen WRA for eligibility, a disclosure statement will describe the components of the interview, and verbal consent will be requested by the data collector before proceeding with the interview. For the intervention trial, signed consent will be required. Printed consent forms prepared in the local language, Afaan Oromo (Oromiffa), will be read aloud by the data collectors to individuals who are considering participation in the study. A participant advocate who is not part of the research team will be present during the consent procedures and will cosign the forms as a witness. The consent form describes how the data will be protected to ensure confidentiality and the possible use of deidentified data and stored biological specimens for future research.

The study protocol was submitted to the institutional review boards (IRB) at the Ethiopian Public Health Institute (EPHI) and the University of California Davis (UC Davis). The EPHI IRB approved the study (including both the preliminary investigations and the intervention trial) on 2 June 2023 (protocol number EPHI-IRB-494-2023). Following its review of the protocol (Project No 2078626-1) and examination of documents from the EPHI IRB, the UC Davis IRB determined on 18 September 2023 that separate approval from UC Davis was not required. The trial protocol has been registered with the ClinicalTrials.gov website (registration number NCT06223854).

Study participants will receive the study salts for free, and they will be compensated in kind with sanitary products, like soaps, and other small (non-monetary) gifts.

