### Intervention

Households of WRA will be randomly assigned to one of three study arms to receive salt fortified with: (1) a lower dose of folic acid+iodine, (2) a higher dose of folic acid+iodine or (3) iodine only (comparator group). Based on the results of preliminary studies of discretionary salt intake in the study communities, the amount of folic acid in the two DFS will be 30 ppm for the lower dose arm and 90 ppm for the higher dose arm to provide average additional folic acid intakes of ~200 μg/day or ~600 μg/day, respectively, in the two folic acid groups. These amounts of additional folic acid intake are intended to span a range of intakes that should increase RBC folate concentration, as indicated by a previous folic acid supplementation trial,^28^ and should not result in excessive folic acid intake.^29^ This dose–response design will also permit subsequent modelling to determine the appropriate level of folic acid fortification needed to achieve a desired RBC folate concentration in the local context. We recognise that minor losses of folic acid may occur during storage of DFS-IoFA ([name], unpublished),^30^ so the target fortification levels account for this. We also note that folic acid is sensitive to different types of cooking, related cooking temperatures and duration of thermal exposure.^31 32^ Nevertheless, most folic acid is retained during cooking of fortified flours and rice, regardless of the type of cooking, and flour fortification programmes have succeeded in reducing NTDs despite the effects of cooking. Thus, we expect to be able to detect a nutritional response to the folic acid-fortified salt.

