**Figure 2 F2:**
[figure not shown]
Example of label for salt container.

Two staff members of EPHI who are not part of the field study team will receive the salts from the producer and a list of study group assignments from the UC Davis statistician who completes the randomisation list. One of these staff members will place a preprinted adhesive label with the participant ID number and bar code on the container to conceal the letter identifying the type of salt. The second staff member will observe the labelling process and confirm that each participant number is affixed to the correct type of salt. The newly labelled containers of salt will then be stored by participant study number for subsequent distribution.

Project staff members will deliver two containers of the study salts (1 kg salt) to the participating households biweekly for a total of 26 weeks. Any households that use more than the initially delivered amount of salt will be able to request additional salt, as needed. At the time of each home visit for salt delivery, the field workers will request the participants to present their study ID cards to confirm that the correct type of salt is being delivered (by matching the participant identification numbers on the card and the containers of salt). Field staff members will explain repeatedly that: (1) the stored salt should be protected from light and extreme temperatures during storage in the home, and (2) the salt is intended only for consumption by members of the household and should not be shared with other households or used for other purposes.

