**Figure 3 F3:**
[figure not shown]
Schedule of data collection activities for individual study participants. *Blood draw 2 will be completed at a randomly assigned time point between weeks 4 and 20 of the intervention period. At the time of each blood draw, anthropometrics and blood pressure will be assessed. 24-hrUC = 24-hour urine collection to assess urinary iodine and sodium excretion; WFR = weighed food record to assess dietary intake.

All women will participate in dietary assessments—conducted as 24-hour, in-home, weighed food records—to assess discretionary salt intake and will collect 24-hour urine specimens for assessment of urinary iodine and sodium excretion. These studies will be carried out on 1 day before the intervention and 1 day between weeks 4 and 24 of the intervention; a randomly selected subset of 40 women in each study arm will complete these studies a second time during the intervention, 1–2 weeks after the first study, to allow for calculation of intraindividual variation in intakes and urinary excretion.^34^ This is necessary to estimate the distributions of usual discretionary salt intake and urinary sodium and iodine excretion of the study population. Procedures for anthropometry; blood pressure measurement; blood and urine collection, processing and analysis; dietary assessments; and assessments of food security and dietary diversity are described as follows.

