### Management of trial

Major decisions on scientific aspects of the trial will be the responsibility of the co-PIs and co-investigators, who will also recruit, train and supervise the other members of the study team. Day-to-day operations will be managed jointly by the field coordinator from EPHI and a postdoctoral research fellow from UC Davis. The field team will be organised into separate domains of activity, including participant screening, enrolment and anthropometry; blood collection and processing; distribution of salt and assessment of compliance; dietary assessment and 24-hour urine collections; blood collection and preliminary processing; laboratory analysis; data analysis; and administration and logistics. Study participants will be recruited over a period of 3 months, and all primary data and specimen collections should be completed within 9 months.

Senior members of the EPHI field team will be involved in different aspects of institutional and community sensitisation, as appropriate. Ministry of Health and other public sector administrators have been contacted at the regional, zonal, woreda and kebele levels to explain the research, address any concerns and facilitate project-related activities. The health facility heads in the study area have authorised data collection activities and access to local health facilities. Separate meetings are being convened with individual (political, religious and traditional) community leaders and potential study participants and their families.

All data collection and laboratory procedures will conform to written instructions compiled in a standard operating procedures manual. A separate statistical analysis plan will be prepared before initiation of the data analysis. Data entry forms will be drafted, field tested and revised accordingly. The forms will be prepared in English, translated into the local language (Oromiffa) and back-translated to English. In most cases, these forms will then be converted to a digital data entry platform, as described above.

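### The before/during change in salt intake can be described, but not reported as an effect of free distribution, because every arm receives free salt

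*Protocol article*

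**What the plan says.** In the protocol article, Study design, study site and randomisation, the paragraph on endpoints ends with an additional aim. "We will also assess the effect of free distribution of salt" is the opening, and the contrast is named in the same sentence: "discretionary salt consumption by monitoring salt intakes and 24-hour urinary sodium excretion before and during the trial". Both the causal target and the comparison that is to answer it are thus fixed in this document.

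The supply is the same for everyone. Under Informed consent: "Study participants will receive the study salts for free". Under Intervention, the arms are listed as "1) a lower dose of folic acid+iodine, (2) a higher dose of folic acid+iodine or (3) iodine only (comparator group", and staff "will deliver two containers of the study salts (1 kg salt) to the participating households biweekly". No group that goes on obtaining its own salt is described.

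The timing of the weighed food records and 24-hour urines is given under Data collection procedures: "These studies will be carried out on 1 day before the intervention and 1 day between weeks 4 and 24 of the intervention". A random subset of 40 women per arm repeats the in-trial day 1 to 2 weeks later. On the calendar: "The intervention was initiated on 30 April 2024 and data collection should be completed by mid-December 2024". Under Management of trial: "Study participants will be recruited over a period of 3 months".

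**The concern.** An effect of free distribution is a contrast between intake with free supply and intake without it over the same period. The trial observes the second state only before enrolment and the first only afterwards. Whatever else changes between those two times enters the same number.

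If intake drifts for another reason, the drift would be reported as something free supply caused. A drift in the opposite direction could equally hide a real effect. This matters for interpretation. The trial is meant to inform a national salt programme and to interpolate a fortification level from the observed distributions (Introduction; Data management and statistical analysis). Whether free supply alters salt use bears on how far the observed intakes carry over to purchased salt.

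**Working it through.** The article gives no sample size or precision figure for this aim, so there is none to reproduce. The check concerns what the design can identify, plus one calendar calculation.

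**1. What the arms contribute.** Write the mean before/during change in any arm as F + C + E + D. F is the effect of free supply, C is calendar drift, E is everything else that starts at enrolment, and D is any effect of the arm's own salt.
- Arm minus arm: (F + C + E + D1) − (F + C + E + D2) = D1 − D2. F cancels, so the randomised contrast says nothing about it. C and E cancel too, which is why the main comparisons are safe.
- All arms pooled: F + C + E + average D. This equals F only if C, E and average D are all zero or known.

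**2. What sits in E.** Set side by side, before and during:
- Weighed food record: same direct observation at both times (Dietary intake assessments). The in-trial day is at least the second time the woman is observed.
- 24-hour urine: same procedure at both times.
- Agreement to use only project salt: operates only during the intervention (Inclusion, exclusion and withdrawal criteria).
- Collection and weighing of leftover salt, with questions on its use, every two weeks: only during (Intervention).

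**3. What sits in C.** Inputs: first start 30 April 2024; in-trial day in weeks 4 to 24; participation 26 weeks; endline blood in weeks 24 to 26; data collection complete by mid-December, taken here as 15 December (an assumption).
- Earliest in-trial day: 30 April + 4 weeks = 28 May. Last in-trial day for that woman: 30 April + 24 weeks = 15 October.
- Latest start if all 26 weeks are completed: 15 December − 26 weeks = 16 June. Her in-trial window: 14 July to 1 December.
- Latest start if she finishes at week 24: 15 December − 24 weeks = 30 June. Her in-trial window: 28 July to 15 December.
- Calendar period in which late starters can still have a baseline day while early starters already have an in-trial day: 28 May to 16 June = 19 days (2.7 weeks), or 28 May to 30 June = 33 days (4.7 weeks).
- As a share of the span of all in-trial days: 19 of 187 days (28 May to 1 December), about 10%; or 33 of 201 days (28 May to 15 December), about 16%.

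These overlaps are upper limits, because they place the baseline day immediately before the start of the intervention. Every woman's own in-trial day falls 4 to 24 weeks into her intervention, so every within-woman contrast crosses calendar time.

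**4. Check against the recruitment period.** Three months of recruitment counted from 30 April would put the last start near 30 July and 26 weeks later at late January 2025, past mid-December. Recruitment that began before 30 April fits the dates, and Management of trial also gives 9 months for all data collection: 15 December − 9 months = 15 March, and 15 March + 3 months = 15 June. That reading is an assumption, but it agrees with a latest start of about 16 June.

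**The case against.** The case on the other side has weight.

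- **The aim is peripheral.** It is a single additional sentence, absent from the main objectives and from the listed primary and secondary outcomes. This stands, and it sets the severity.
- **The comparison is stated openly as before and during, and the change can be estimated.** This stands. A reader might infer that the trial can say nothing about change in salt use; that is too strong. Only the causal label is unsupported.
- **Observation is largely the same at both times.** A reader might infer that the change is an artefact of being watched. The weighed records and urine collections use the same methods before and during, so only the added biweekly visits, the salt-use agreement and repeat observation differ.
- **Season is not discussed anywhere.** This stands. Calendar confounding is inferred from the dates, and nothing in the article shows that discretionary salt varies over the year here.
- **Time trends can be examined.** In-trial days are spread over weeks 4 to 24 and disappearance is measured biweekly. This shows trends while on free salt. It cannot separate a step at enrolment, and disappearance is defined for project-supplied salt, so it has no baseline value.
- **The article already calls the trial a hybrid and says salt is not acquired under usual market conditions.** That discloses limited generalisability. It does not say that the before/during change fails to isolate the free-supply component.
- **The analysis plan is a separate document.** The absence of a model for this aim is therefore no defect. The aim and its contrast are nonetheless fixed in the article.

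**Conclusion.** The point holds as a matter of identification and wording. Free supply does not vary between arms, no concurrent group lacks it, and the before/during change mixes it with calendar time and with other things that begin at enrolment. Reading that change as the effect of free distribution requires all of these to be nil, which the design cannot show.

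No size can be put on the possible bias. A reader might turn the reported interval of 4.1 to 10.2 g/day around the 6.6 g median into a standard deviation and derive a drift that would reach significance. The documents do not support that step. Safety considerations describes 10.2 g as the 95th percentile of usual intake, so the implied spread is not that of one-day records. A drift equal to the critical difference would be significant only about half the time. No drift figure is given at all.

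Severity is minor. The randomised comparisons of salt consumption, folate, iodine and serious adverse events are not affected. The overlap of about 3 to 5 weeks rests on taking mid-December as 15 December and on women completing 24 to 26 weeks by then.

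**What to change.** Restate the aim as: to describe the uncontrolled change in women's discretionary salt intake and 24-hour urinary sodium from before to during the trial. Add to the limitations that all arms received free salt, that no concurrent group without it was measured, and that the change may also reflect calendar time, the agreement to use only project salt, biweekly weighing and questioning, and repeat observation. Do not report the result as an effect of free distribution.

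A model with calendar terms and an on-trial indicator may be added as a sensitivity analysis, labelled fragile. With about 3 to 5 weeks of overlap the two are nearly collinear, and the separation would rest largely on comparing early with late starters.

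The cost is a change of wording in the analysis plan and the report, and a weaker claim. No new data are needed. Only a concurrent group without free salt would support the causal wording, and the intervention had already begun by the article's own dates, so the restatement is the proportionate remedy.
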